**Identification of primary and secondary outcomes**

Follow-up will begin at index date until the first recorded date of incident CRC, proctocolectomy, emigration, death, or end of follow-up (Dec, 2019). A patient who had a colectomy but had an intact rectum will be considered at risk of rectal cancer until proctectomy (see **Table 2** for procedure codes). The primary outcome is incident CRC (see **Table 2** for ICD codes), while secondary outcomes are CRC-related mortality and all-cause mortality (see **Table 2** for ICD codes).

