**Subgroup analyses and sensitivity analyses**

We will assess whether the associations vary by the following factors: age at the index date (<60 or ≥60 years), sex, calendar period for IBD diagnosis (1969-1999 or 2000-2018), educational attainment (0-9, 10-12, ≥13 years, or “missing”), IBD subtype (CD or UC), age at IBD diagnosis (<50 or ≥50 years), duration of IBD (<10 or ≥10 years), type of statins initially treated, and type of CRC (colon cancer or rectal cancer).

Several sensitivity analyses will be conducted. First, we will construct a model in which covariates will adjusted as time-varying variables. Second, we will exclude individuals with a history of CVD before statin initiation. Third, we will discard the first year and then first two years of follow-up from the analysis. Fourth, we will evaluate the potential influence from unmeasured confounding by calculating E-values^14^. Finally, we will perform a negative control analysis using fracture as a negative control outcome to assess potential biases in our study^15^.

Data analyses will be performed using SAS version 9.4, Stata (version 16.1), and R version 3.6.0.

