| Dexamethasone | H02AB02 |
| Methylprednisolone | H02AB04 |
| Prednisolone | H02AB06 |
| Prednisone | H02AB07 |
| Hydrocortisone | H02AB09 |
| Cortisone | H02AB10 |
| Systemic aminosalicylates (5-ASA) |  |
| Sulfasalazine | A07EC01 |
| Mesalazine | A07EC02 |
| Olsalazine | A07EC03 |
| Balsalazide | A07EC04 |
| Rectal aminosalicylates (5-ASA) |  |
| Mesalazine | A07EC02 |
| Corticosteroids acting locally |  |
| Hydrocortisone | A07EA02 |
| Budesonide | A07EA06 |
| Non-aspirin anti-platelet medications | B01AC excluding aspirin (B01AC06) |
| Aspirin | B01AC06 |
| Non-statin lipid lowering medications | C10AB, C10AC, C10AD, C10AX01-14 |
| Anti-diabetic medications | A10 |
| Anticoagulation medications | B01AA, B01AE, B01AF, B01AX |
| Anti-arrhythmias medications | C01BA, C01BB, C01BC, C01BD, C01BG |
| ATC: Anatomical Therapeutic Chemical; CRC: colorectal cancer; HIV/AIDS: human immunodeficiency virus/ acquired immunodeficiency syndrome; ICD: the International Classification of Disease. | |
| ^a^ ATC codes will be identified from the Prescribed Drug Register; ICD codes and procedure codes will be identified from the National Patient Register. | |
| ^b^ Incident CRC will be ascertained from the Cancer Register, while CRC-related mortality will be ascertained from the Cause of Death Register. In the Cancer Register, all ICD-8, ICD-9, and ICD-10 codes were back-translated to ICD-7. | |
| ^c^ Not at risk of colorectal cancer. | |
| ^d^ Only at risk of rectal cancer. | |
| ^e^ Not at risk of colorectal cancer. | |

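### A colorectal cancer already present at bowel surgery but recorded after it may not count as a primary event, and same-day cancer and surgery records have no precedence rule

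*SAP*

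**What the plan says.** The primary outcome is defined under Identification of primary and secondary outcomes: "The primary outcome is incident CRC (see Table 2 for ICD codes"). The same section sets the end of follow-up: "Follow-up will begin at index date until the first recorded date of incident CRC, proctocolectomy, emigration, death, or end of follow-up (Dec, 2019"). For a less extensive operation it adds: "A patient who had a colectomy but had an intact rectum will be considered at risk of rectal cancer until proctectomy".

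The Table 2 footnotes repeat the logic. Footnotes c (proctocolectomy) and e (rectum amputation after a colectomy that left the rectum) read "Not at risk of colorectal cancer". Footnote d (colectomy with intact rectum) reads "Only at risk of rectal cancer".

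The two kinds of date come from two sources. On the outcome: "Incident CRC will be ascertained from the Cancer Register, while CRC-related mortality will be ascertained from the Cause of Death Register". On operations: "ICD codes and procedure codes will be identified from the National Patient Register". The SAP does not say which Cancer Register date is meant (sampling, diagnosis or registration). It gives no rule for a cancer and an operation recorded on the same day, and no window after surgery.

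Patients with a colectomy or a cancer before the index date are excluded under Two-step matching process. The operations at issue therefore fall within follow-up.

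**The concern.** It is reasonable to stop counting risk time for an organ that has been removed: no new cancer can arise there. That reasoning does not cover a cancer already in the specimen. Such a cancer arose during at-risk time and belongs to the primary outcome. If it is established only by examining the specimen, the finding cannot precede the operation, so its record may carry the same date or a later one. Because the rule follows the order of recorded dates, a later date turns a true primary event into a non-event. This is so whether surgery is handled as censoring or as a competing event.

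At stake are the CRC event count, the incidence rates and their difference, the cumulative incidence and the 10-year NNT. The as-treated analysis inherits the same end-of-follow-up rule. The colon and rectal analyses would miss the same cases, as would the sidedness and stage analyses that the SAP lists as not prespecified. For a same-day record, two programmers following this SAP could code the same patient differently.

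**Working it through.** The SAP gives no event count or loss figure on this point, so there is nothing of its own to reproduce. The check has two parts.

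**1. Applying the written rule to the possible date orders**

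| Operation (Table 2) | CRC dated before surgery | Same date | CRC dated after surgery |
|---|---|---|---|
| Proctocolectomy (footnote c) | counted | undefined | not counted |
| Colectomy, rectum intact (footnote d), colon cancer | counted | undefined | not counted |
| Colectomy, rectum intact (footnote d), rectal cancer | counted | counted | counted until proctectomy |
| Rectum amputation after such a colectomy (footnote e), rectal cancer | counted | undefined | not counted |
| Operation not in Table 2 | counted | counted | counted |

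As an invented example, take a proctocolectomy on 1 March whose specimen shows a cancer carrying a register date of 8 March. Follow-up ended on 1 March, so the patient is not a case. If the register date used were 1 March, the SAP would not say which record prevails.

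No other analysis covers this. The nearest time-related one is "Third, we will discard the first year and then first two years of follow-up from the analysis". It removes time after the index date and leaves the handling of dates around surgery as it was. The other sensitivity analyses (time-varying covariates, exclusion of prior cardiovascular disease, E-values, the fracture negative control and the added exclusion of diabetes) do not address it either.

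**2. Size, under assumed shares**

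Let f be the share of all CRCs that are lost. These are cancers already present at surgery, in an operation that ends risk for that site, and dated strictly after it. The SAP gives no value, so f is an assumption. Assume also that CRC is uncommon enough for person-time to be hardly affected, and that f is constant over follow-up.

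- Observed rate = true rate × (1 − f).
- With equal f in both arms, observed rate difference = true difference × (1 − f).
- NNT is the inverse of an absolute difference, so observed NNT = true NNT × 1/(1 − f).
- Observed HR ≈ true HR × (1 − f in users)/(1 − f in non-users).

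| Assumed f, equal in both arms | Rate difference × | NNT × | HR × |
|---|---|---|---|
| 2% | 0.98 | 1/0.98 = 1.02 | 1.00 |
| 5% | 0.95 | 1/0.95 = 1.05 | 1.00 |
| 10% | 0.90 | 1/0.90 = 1.11 | 1.00 |
| 15% | 0.85 | 1/0.85 = 1.18 | 1.00 |

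If the loss differed between arms, the HR would move. With 5% lost in users and 10% in non-users, a true HR of 1.00 would read 0.95/0.90 = 1.06. The reverse gives 0.90/0.95 = 0.95. These two figures show only how the formula behaves; the SAP supports neither split.

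**The case against.** The strongest reply is that the loss is conditional. If the Cancer Register date used is the date of the specimen, a cancer found at surgery is a same-day tie and not a later record. Incident CRC is the primary outcome and stands first in the list of end points, so counting it on a tie is a natural reading. This stands in part. The document does not show that such cancers are lost, only that they may be. But the SAP does not name the date, and a natural reading is not a rule.

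Second, only the operations in Table 2 matter. Other resections do not end follow-up, and after a colectomy that leaves the rectum, follow-up for rectal cancer continues. This stands and limits the point.

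Third, a reader might take the share of CRCs first found at surgery as the share lost. That share is only an upper bound, because cancers dated before the operation count and same-day records are undefined.

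Fourth, a reader might infer a biased hazard ratio. The SAP does not support this. It gives no evidence of different loss by arm. The arms are matched on sex, IBD subtype, and age and calendar period at IBD diagnosis, and by propensity score on IBD duration, healthcare visits and IBD medications, among others. Matching makes a large difference less likely but cannot rule it out.

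Fifth, version 3 of the SAP follows external review, so redefining the primary event now could look post hoc. That is a fair reason to keep the no-window result in view. It is not a reason to leave the cancer date and the tie undefined.

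**Conclusion.** The point holds in a limited form. As written, the SAP may fail to count a CRC that was already present at surgery if its recorded date falls after a proctocolectomy or after a proctectomy that follows a colectomy. The same applies to a colon cancer dated after a colectomy with intact rectum. A same-day record has no precedence rule. This is more than missing detail, because the stated rule can turn true primary events into non-events and no planned analysis tests it.

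The size is unknown. Under an assumed equal loss of 2% to 15%, the absolute measures shrink in proportion and the NNT is overstated by about 2% to 18%, with the HR about unchanged. How often cancers are dated after the operation depends on a register date that the SAP does not specify. It should be corrected, but the document does not show that the planned hazard ratio would be wrong.

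**What to change.** In Identification of primary and secondary outcomes, and in footnotes c to e of Table 2:

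1. State which Cancer Register date defines incident CRC.
2. State that CRC takes precedence over surgery recorded on the same date.
3. Count a CRC recorded within a prespecified short window after a Table 2 operation (for example 90 days) as an event dated at the surgery. Include colon cancer after a colectomy that leaves the rectum. Apply the rule identically in both arms.
4. Add a sensitivity analysis with other window lengths, including no window, and report the number of CRCs reclassified in each arm. That count would show whether any loss differs between arms.

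The cost is a few sentences and a small change to the outcome program. The downside is a short look-ahead after surgery, with a window length that is a convention; the document gives no basis for 90 days over another value. If outcome results have already been seen, the change should be labelled as made after that point, with the no-window result shown beside it.

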**Two-step matching process**

A two-step matching process will be applied to establish the cohort. In the direct matching step, statin users and non-statin users will be matched on age at IBD diagnosis (<18, 18-<40, 40-<60, and ≥60), sex, IBD subtype (CD or UC), and calendar year at IBD diagnosis (1969-1989, 1990-1999, 2000-2009, 2010-2018). IBD-unclassified will not be considered in this project due to diagnostic uncertainty. To ensure similar opportunities for care and treatment^10^, non-statin users should have a random drug prescription (except IBD medications, see **Table 2** for ATC codes) within three months before or after the start date of statin treatment in the matched statin users. All identified non-statin users will be assigned the same index date as the index statin user. We will exclude individuals who had a record of migration, received a colectomy, or had a diagnosis of any of the following diseases before the index date: cancers, human immunodeficiency virus/ acquired immunodeficiency syndrome, primary immunodeficiency disease, end-stage renal disease, severe liver failure, and any organ transplantation (see **Table 2** for procedure and ICD codes).

In the propensity score matching step, statin users and non-statin users will be matched in a 1:1 ratio by using a greedy nearest-neighbor matching algorithm without replacement, with a caliper of 0.2 standard deviation of the logit of the propensity score^11^. A logistic regression model will be used to calculate the propensity score after adjusting for the below demographic and socioeconomic characteristics, comorbidities, and co-medications identified up to and including the index date.

- Age at IBD diagnosis, years (continuous);
- Duration of IBD, years (continuous);
- Number of healthcare visits (continuous);
- Country of birth (Nordic countries or others);
- Education (0-9, 10-12, ≥13 years, or missing);
- Comorbidities (yes/no, see Table 2 for detail): gastrointestinal diseases, intestinal infections, cardiovascular diseases, obesity/dyslipidemia, type 1 and type 2 diabetes, autoimmune diseases, obstructive sleep apnea, chronic obstructive pulmonary disease, and myositis;
- Medications (yes/no, see Table 2 for detail): antibiotics, proton pump inhibitor, antiviral medications, IBD medications, non-aspirin anti-platelet medications, aspirin, non-statin lipid lowering medications, anti-diabetic medications, anticoagulation medications, and anti-arrhythmias medications.

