**STATISTICAL ANALYSES**

Incidence rates and their differences with 95% confidence intervals (CIs) for incident CRC, CRC-related mortality, and all-cause mortality will be calculated using Poisson regression. To account for competing risk, we will apply subdistribution hazard model to estimate hazard ratios (HRs) and 95% CIs, using time since index date as the underlying time scale. Cumulative incidence function will be applied to estimate the cumulative incidence of the primary and secondary outcomes.

We will calculate the number needed to treat (NNT)^12^ to avoid one event at 10-year since it is the most commonly used time period for CRC^13^.

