**Secondary analyses**

Three secondary analyses will be conducted. First, to assess the relationship between continuous statin treatment and outcomes, we will apply an as-treated analysis where we further censor the follow-up at the end of the first treatment episode, in addition to the abovementioned censoring criteria. Second, to evaluate whether cumulative duration of statin use is associated with the outcomes, we will apply a nested case-control study in statin users. Using the method of incidence density sampling, for each case exposed to statin and with later studied outcomes, we will randomly select up to five statin users who did not develop the interested outcomes (controls). They will be individually matched on age at index date, gender, IBD subtype, IBD duration, and duration of follow-up. Conditional logistic regression will be used to estimate odds ratios (ORs) with 95% CIs. The cumulative duration of statin use will be assessed between first prescription and end of follow-up, and categorized into categories (30 days-<1 year (reference group), 1-<2 years, 2-<5 years, and ≥5 years cDDD). Trends in the dose-response association will be tested by using the duration strata as an independent variable in the model. Third, we will repeat the main analysis without accounting for competing risks.

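### The only follow-up rule stops at CRC diagnosis or proctocolectomy, so CRC-related deaths are almost never counted and all-cause deaths are selectively truncated

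*SAP*

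**What the plan says.** The SAP section Identification of primary and secondary outcomes sets the observation period: "Follow-up will begin at index date until the first recorded date of incident CRC, proctocolectomy, emigration, death, or end of follow-up (Dec, 2019". The next sentence adds one refinement, for patients with a colectomy and a retained rectum, and it concerns rectal cancer risk only. The same paragraph then makes incident CRC the primary outcome, "while secondary outcomes are CRC-related mortality and all-cause mortality".

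The section Statistical analyses applies its methods to all three outcomes and gives no other end date. Rates and rate differences "for incident CRC, CRC-related mortality, and all-cause mortality will be calculated using Poisson regression". On hazard ratios it says: "To account for competing risk, we will apply subdistribution hazard model to estimate hazard ratios (HRs) and 95% CIs", without naming the competing event for any outcome. It adds: "Cumulative incidence function will be applied to estimate the cumulative incidence of the primary and secondary outcomes".

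Under Secondary analyses, the as-treated analysis stops at the end of the first treatment episode "in addition to the abovementioned censoring criteria". That refers back to the same rule and does not vary it by outcome.

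Two other statements bear on the point. Two-step matching process excludes anyone who "had a diagnosis of any of the following diseases before the index date: cancers" (among other conditions). A footnote to Table 2 takes incident CRC from the Cancer Register and CRC-related death from the Cause of Death Register.

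**The concern.** Stopping at CRC or proctocolectomy suits incident CRC: the first is the event itself, and the second removes the tissue at risk. Neither suits a death outcome. A patient with CRC is still at risk of dying from it, and a patient without a colon is still at risk of dying from anything.

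Both mortality outcomes appear in the study objectives and in the hypothesis. If a programmer builds one end date from this section and uses it throughout, the rates, hazard ratio and cumulative incidence for CRC-related death, and any 10-year number needed to treat for it, would rest on a small, atypical residue of cases. The all-cause comparison would lose deaths after CRC, and with them any difference between the groups that acts through CRC incidence or survival after CRC. The problem carries into the nested case-control study, which matches on length of follow-up and measures exposure up to its end.

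**Working it through.** The SAP states no event count or expected rate on this point, so there is no figure of its own to reproduce. The main conclusion comes from reading the rule against each outcome. The arithmetic only illustrates size.

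**Step 1. The rule against each outcome**

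| Outcome | Effect of stopping at CRC | Effect of stopping at proctocolectomy |
| --- | --- | --- |
| Incident CRC | Is the event | Ends the risk; reasonable |
| CRC-related death | Follow-up ends before the event | Ends follow-up although death is still possible |
| All-cause death | Drops every later death | Drops every later death |

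Because earlier cancer is an exclusion, a CRC death should come from a cancer arising after the index date. Registration normally precedes death, so the patient has already left follow-up. The exceptions are cancers absent from the Cancer Register and cancers first recorded on the date of death.

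**Step 2. Inputs for size**

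From the SAP: the Cancer Register holds more than 96% of incident cancers (all types), and the horizon for the number needed to treat is 10 years.

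Assumed, not in the SAP:
- CRC rate c: 1 to 3 per 1,000 person-years
- proctocolectomy rate p: 2 to 10 per 1,000
- non-CRC death rate d: 15 to 30 per 1,000
- CRC-specific death hazard after diagnosis h: 0.08 to 0.20 per year
- CRC first recorded at death: 0% to 3%
- constant hazards; unregistered cancers as fatal as registered ones; proctocolectomy leaves the non-CRC death rate unchanged

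**Step 3. Share of 10-year CRC deaths counted**

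- Every CRC registered before death: 0%.
- 4% of CRC unregistered: about 4%, slightly reduced by proctocolectomy between cancer and death. A simulation of 2,000,000 patients per scenario gave 3.3% to 4.6%, the spread being largely simulation noise.
- A further 3% first recorded at death: about 4% + 3% = 7%; simulated 6.4% to 7.7%.

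**Step 4. Share of 10-year all-cause deaths counted (all CRC registered)**

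Deaths counted under the rule: d/(c+p+d) × [1 − exp(−(c+p+d) × 10)].

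All deaths: 1 − exp(−10d) × (1 − P). Here P is the probability of CRC followed by CRC death within 10 years, ignoring other deaths. With k = c + p, P = c × {[1 − exp(−10k)]/k − exp(−10h) × [exp(10(h−k)) − 1]/(h−k)}.

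- Largest loss (c 0.003, p 0.010, d 0.015, h 0.20). Counted: 0.015/0.028 × (1 − exp(−0.28)) = 0.5357 × 0.2442 = 0.1308. P = 0.0162. All deaths: 1 − 0.8607 × 0.9838 = 0.1532. Share counted: 0.1308/0.1532 = 85.4%, so 14.6% are lost.
- Smallest loss (c 0.001, p 0.002, d 0.030, h 0.08). Counted: 0.030/0.033 × (1 − exp(−0.33)) = 0.9091 × 0.2811 = 0.2555. P = 0.0031. All deaths: 1 − 0.7408 × 0.9969 = 0.2615. Share counted: 97.7%, so 2.3% are lost.

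The simulation agrees: 85% to 98% of deaths counted. If the mortality outcomes are followed past CRC and proctocolectomy, all of these deaths count. The 10-year risks under the same assumptions are then about 0.2% to 1.5% for CRC death and 14% to 27% for any death.

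**The case against.** The best defence is that the rule was meant for the primary outcome only. Its content fits incident CRC, the retained-rectum sentence concerns cancer risk, the Table 2 footnotes describe the procedures by remaining cancer risk, and the mortality outcomes are named afterwards. This may well be what the authors intended. But the SAP does not say so. The heading covers the secondary outcomes, no other end date is given, and the as-treated analysis reuses the rule without distinguishing outcomes. Intent makes the correction easy; it does not remove the need for it.

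Three stronger readings are tempting, and the SAP does not support them.

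- A reader might infer that the all-cause hypothesis also cannot be tested. It can: most deaths still fall within follow-up. The result is a selectively truncated quantity.
- A reader might infer that a subdistribution model for all-cause death must treat CRC or proctocolectomy as precluding death. The SAP names neither as a competing event for death. With no competing event the model reduces to an ordinary Cox model, and the cumulative incidence function to one minus Kaplan-Meier. The third secondary analysis also drops the competing-risk adjustment. The end date is the fault.
- A reader might take the register's completeness to mean that at most 4% of CRC deaths could be counted. That figure is for incident cancers of all types, not CRC deaths, and cancers first recorded at death add to it. Only the qualitative statement, almost none, is secure.

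**Conclusion.** Wrong as written. For CRC-related mortality the loss is nearly complete. That follows from the order of diagnosis and death together with the exclusion of earlier cancer, and it does not depend on the assumed rates; the illustrations give 0% to about 8% of CRC deaths counted. For all-cause mortality the loss is partial but selective, about 2% to 15% of 10-year deaths. That range rests wholly on rates the SAP does not give and should be read as an order of magnitude. The incident CRC analysis is not affected by this point. The finding concerns what the text instructs, and it makes no claim that the authors meant one end date for every outcome.

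**What to change.** Replace the single rule with one end of follow-up per outcome:

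- **Incident CRC:** keep the current rule.
- **CRC-related mortality:** follow from index date to CRC death, with death from other causes as the competing event. Censor at emigration or December 2019, and not at CRC diagnosis or proctocolectomy.
- **All-cause mortality:** follow from index date to any death, censoring only at emigration or December 2019. State that there is no competing event, so the model is an ordinary Cox model.

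Make the back-reference in the as-treated analysis, and the follow-up duration used in the nested case-control study, point to the rule for the outcome concerned. The cost is a few sentences in the SAP and outcome-specific end-date variables. The registers already in use hold the dates, so no new data are needed.
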